**a. Location**

We have partnered with four school districts for this project (see letters of support from superintendents and principals in these districts in Appendix A) Elgin ISD, Manor ISD, Georgetown ISD, and Del Valle ISD. These districts were selected because of their: 1) high proportion of Hispanic children (>50%); 2) high proportion of children participating in the free and reduced lunch (FRL) program (>50%); 3) high proportion of overweight or obese children; 4) location within 60 miles of UT-Austin campus; and 5) interest and support in a garden/nutrition school program. There are 18 schools within these school districts that meet the inclusion criteria. Sixteen out of the 18 schools will be randomly selected from this sampling frame to allocate to the intervention or control arms and the two schools remaining will be used for replacement if a school declines to participate.

Data collection and related study activities will occur at these schools within each school district.

**b. Resources**

External funds from the National Institutes of Health (NIH) will support this project. Notice of award is pending, but this grant received a fundable score and funding is highly likely. Earliest possible funding start date would be April 1st, 2015. Of note, IRB approval is needed for Just-In-Time NIH request.

**c. Study Timeline**

The intervention will run in a series of three waves across four academic school years in Years 2-5 (see **Table 1**). Waves 1 and 2 (**W1** and **W2**) will each include six schools (3 intervention (INT) and 3 control (CON) schools), and Wave (**W3**) will consist of four schools (2 INT and 2 CON).

| Table 1: General design and timeline of study                                                                                                                                                                                                                                                                                     |                                                                                                                                                                                                                                                                                     |                                                                                                                                                                                                                                |                                                               |
|-----------------------------------------------------------------------------------------------------------------------------------------------------------------------------------------------------------------------------------------------------------------------------------------------------------------------------------|-------------------------------------------------------------------------------------------------------------------------------------------------------------------------------------------------------------------------------------------------------------------------------------|--------------------------------------------------------------------------------------------------------------------------------------------------------------------------------------------------------------------------------|---------------------------------------------------------------|
| Year                                                                                                                                                                                                                                                                                                                              | Fall                                                                                                                                                                                                                                                                                | Spring                                                                                                                                                                                                                         | Summer                                                        |
| 1                                                                                                                                                                                                                                                                                                                                 | -Obtain UT-Austin and school district IRB approvals; Hold stakeholders meetings to plan implementation of Sprouts curriculum at each of the schools; Set up database; and Hire and train staff; Randomly allocate schools into INT/CON and into waves; Adapt and modify curriculum. |                                                                                                                                                                                                                                | -Build W1-INT gardens                                  |
| 2                                                                                                                                                                                                                                                                                                                                 | - W1 baseline measurements
-Implement W1-INT Sprouts program                                                                                                                                                                                                       | -Complete W1-INT Sprouts
- W1 post-intervention measurements                                                                                                                                                  | -Build W1-CON gardens
-Build W2-INT gardens  |
| 3                                                                                                                                                                                                                                                                                                                                 | -Host train the trainer workshops for W1-INT
-Implement W1-CON Sprouts program
- W2 baseline measurements
-Implement W2-INT Sprouts program                                                                                                    | -Complete W1-CON Sprouts program
-Complete W2-INT Sprouts program
- W2 post-intervention measurements
-Collect sustainability data in W1-INT                                              | -Build W2-CON gardens -
Build W3-INT gardens |
| 4                                                                                                                                                                                                                                                                                                                                 | -Host train the trainer workshops for W2-INT
-Implement W2-CON Sprouts program
- W3 baseline measurements
-Implement W3-INT Sprouts program                                                                                                    | -Complete W2-CON Sprouts program
-Complete W3 Sprouts program
- W3 post-intervention measurements
-Collect sustainability data in W1-CON
-Collect sustainability data in W2-INT | -Build W3-CON gardens                                  |
| 5                                                                                                                                                                                                                                                                                                                                 | -Implement W3-CON Sprouts program; Host train the trainer workshops for W3 ; Collect sustainability data in W3-INT ; Host the Results Dissemination Workshop; Data entry, cleaning, and analyses; Manuscript and subsequent grant preparation;                 |                                                                                                                                                                                                                                |                                                               |
| Of note: Consenting and measurements in the fall will occur the first 2 weeks of school, and measurements in the spring will occur during the last 2 weeks of school. Data entry, cleaning, and analyses and manuscript preparation will be done continuously in Years 2-5. INT=Intervention schools; CON=Control schools. |                                                                                                                                                                                                                                                                                     |                                                                                                                                                                                                                                |                                                               |

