measurements from baseline to end of study. We assumed that a cluster average size of 127 children per school would have pre and post measurements for vegetable intake, BMI z-scores, and waist circumference but only 60 children per school for blood glucose and insulin values. **Table 2** presents the minimum number of schools needed for power of 80% and 90% for the children's primary outcomes using a type I error of 0.05 and 0.01, a two-sided test, and assuming equal allocation between the two arms. The variance ( $\sigma^2$ ) within schools and the intraclass correlation coefficient (ICC) to estimate the sample size were obtained from the R21 pilot study. Therefore, with six schools and 60 children per school with blood draws, 360 children are needed, and given our preliminary data and attrition rates, we will have enough power to detect the effect size of a decrease in 2.13 mg/dL in fasting glucose. For the children, we will also have enough power to detect an effect size above 0.5 in vegetable (serv/d) intake, a decrease of 0.065 in BMI z-scores, a decrease of at least 0.02 cm in waist circumference, and a decrease of at least 12  $\mu$ U/ml in fasting insulin. **For Aim 2**, we estimate the power of this study for the parents using vegetable intake and availability from Castro et al using the same powers and type I error levels as we used for the

children as well as the R21 pilot data for the variance and ICC. Among the parents, we will have enough power to detect an effect size above 0.5 vegetable intake (serv/d) (**Table 2**).

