#### **e. Recruitment**

A flow chart depicting the study participants through the study appears in **Figure 1**. Sixteen elementary schools will be allocated to either TX Sprouts intervention (n=8 schools) or Control group (n=8 schools). The schools from the sampling frame average approximately 300 3rd-5th grade students for a total of 4,800 3rd-5th grade students. All participants and their parents will have to sign assent and consent forms, approved by UT-Austin's Institutional Review Board. Based on previous intervention work with Hispanic communities, we anticipate ~50% of parents will consent for their children to participate, and their children will complete all the baseline measures (n=2,400). We anticipate 15% attrition at post-intervention measurement due to parents/students moving away or being sick or absent from school, which would mean that 2,040 children (or 127 children per school) would complete the post-testing measures in one school year. Based on blood draw participation rates in LA Sprouts, we anticipate that 50% of participating children (n=1,200) will also participate in the blood draws at pre-intervention and 40% (n=960 or 60 per school) at post-intervention.

Important components of our recruitment and retention strategy developed from numerous years of research with Hispanic children/families include: 1) bilingual staff, 2) Spanish and English forms/questionnaires written at a 3rd grade reading level, and 3) incentives for participation.

We will attempt to recruit approximately 10-15 school stakeholders (i.e., teachers, principals, administration staff) and 5-10 GLCs members to conduct structured interviews with over sustainability issue. The principals at each school will likely help recruit these individuals.

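### The stated school allocation balances arms only within wave, not on district or free/reduced-lunch share; with 8 schools per arm chance imbalance is likely, and cheap to prevent before allocation

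*Protocol*

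**What the plan says.** Section 4.a (Location) describes one sampling frame across districts: "We have partnered with four school districts for this project" and "There are 18 schools within these school districts that meet the inclusion criteria". It continues: "Sixteen out of the 18 schools will be randomly selected from this sampling frame to allocate to the intervention or control arms", with the other two held as replacements. Table 1 in section 4.c gives the allocation step: "Randomly allocate schools into INT/CON and into waves".

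Section 6.e (Recruitment) fixes 8 schools per arm. Section 4.c fixes arm numbers by wave: Waves 1 and 2 "will each include six schools (3 intervention (INT) and 3 control (CON) schools"), and Wave 3 "will consist of four schools (2 INT and 2 CON"). No other restriction is stated.

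Sections 4 and 4.a name percent Hispanic, percent free/reduced lunch and childhood overweight or obesity among the selection criteria, so these are available before allocation. The Data Analyses paragraph gives the primary model as arm (fixed), school (random) and error. Percent free/reduced lunch and wave enter only exploratory interaction tests; district does not appear in the analysis.

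**The concern.** With 16 schools, simple random allocation can leave the arms visibly unlike on characteristics known before the draw. A district might contribute only to one arm, or the poorer schools might cluster in one arm. More children per school does not cure this, because the imbalance lies between schools.

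At stake are the credibility of the comparison and, for outcomes with substantial between-school variance, some precision. The step is also irreversible: allocation is a Year 1 task, before any baseline measurement, so a later analysis plan can adjust for a poor draw but cannot undo it.

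**Working it through.** **1. The plan's own figure.** Schools per arm = 2σ²[1+(m−1)ICC](z₀.₉₇₅+z₀.₈₀)²/(m d²), from Table 2. For glucose (σ²=40.86, m=60, ICC=0.001, d=2.133): 2×40.86×1.059×7.849/(60×4.550) = 2.49, so 3 per arm and 6 in total, as stated. The same formula gives the stated 4 for BMI z and 12 for waist (80% power, alpha 0.05). Vegetable intake and insulin do not reproduce from their printed variances, but only the ICCs and cluster sizes are needed below. The calculation rests on "using a type I error of 0.05 and 0.01, a two-sided test, and assuming equal allocation between the two arms" and contains no balancing factor.

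**2. Chance that a district lies wholly in one arm.** Schools go to waves at random as well, so all C(16,8) = 12,870 arm allocations are equally likely. For one district with s of the 16 schools the probability is 2×C(16−s,8)/12,870:
- s=2: 2×3003/12,870 = 46.7%
- s=3: 2×1287/12,870 = 20.0%
- s=4: 2×495/12,870 = 7.7%
- s=5: 2×165/12,870 = 2.6%

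District sizes are not in the Protocol. Enumerating every split of 16 schools over four districts with at least two schools each, the chance that some district is wholly in one arm is 24.3% at the least (4/4/4/4). Simulating the full scheme (16 drawn from 18, waves of 6/6/4, half per arm) for assumed splits of the 18:

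| Assumed split | Some district with ≥2 drawn schools in one arm | Some district with ≥4 drawn schools in one arm | Arm counts differ by ≥3 in some district |
|---|---|---|---|
| 5/5/4/4 | 32% | 16% | 44% |
| 6/5/4/3 | 41% | 10% | 45% |
| 7/5/3/3 | 49% | 5% | 47% |
| 8/4/3/3 | 54% | 4% | 44% |

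The high figures in the second column come mainly from districts contributing two or three schools.

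**3. Where between-school variance matters.** Between-school share of the variance of a school mean = ICC/[ICC+(1−ICC)/m]:
- Vegetable intake: 0.071/(0.071+0.929/127) = 0.907
- Waist: 0.019/(0.019+0.981/127) = 0.711
- Insulin: 0.554/(0.554+0.446/60) = 0.987
- Glucose: 0.001/(0.001+0.999/60) = 0.057
- BMI z: 0.002/(0.002+0.998/127) = 0.203

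The sample-size section works on change from baseline, so these ICCs are taken to refer to change.

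**4. Precision if the balancing factor is also fitted.** Let f be the share of between-school variance in change that the factor explains. It is unknown; 10% and 20% are assumptions. The ratio of detectable differences at 80% power is √(1 − f×share) times a df penalty. The t multiplier (97.5% plus 80% points) is 3.013 on 14 df, 3.030 on 13 and 3.077 on 11. The penalty is therefore 1.006 for one term and 1.021 for three district terms.

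| Outcome | 1 df, f=10% | 1 df, f=20% | 3 df, f=10% | 3 df, f=20% |
|---|---|---|---|---|
| Vegetable intake | 0.959 | 0.910 | 0.974 | 0.924 |
| Waist | 0.969 | 0.932 | 0.984 | 0.946 |
| Insulin | 0.955 | 0.901 | 0.969 | 0.915 |
| BMI z | 0.996 | 0.985 | 1.011 | 1.000 |
| Glucose | 1.003 | 1.000 | 1.018 | 1.015 |

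Values below 1 are gains. Fitting district is a slight loss for glucose and gives nothing for BMI z at these shares.

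**5. Feasibility of a constraint.** For a fixed wave assignment there are 20×20×6 = 2,400 arm allocations. Requiring arm counts to differ by at most one school in every district, with an illustrative limit of 0.3 SD on mean lunch share, leaves a median of about 170 to 210.

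**The case against.** The allocation sentence is one entry in a timeline table, not a randomisation section. Stratified or constrained allocation is also random, so the Protocol is silent on further restriction rather than excluding it, and it does balance arms within wave. That stands, and the point is worded accordingly. But the wave-by-arm counts are set out exactly and nothing else is, so a team following the text would apply no other constraint.

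Three stronger readings are tempting and are not supported:
- *The allocation biases the effect.* It does not. Random allocation is unbiased; the cost is chance imbalance in the one draw made.
- *A district or poverty difference passes straight into the arm difference.* Outcomes are analysed as changes from baseline, so stable differences in level largely cancel. Only differences in change over the school year matter.
- *The allocation sentence itself gives away a large amount of precision.* The gains in step 4 come from adjustment in the model; balancing the allocation adds little to them. They depend on an explained share that the Protocol does not give, and the df cost must be counted.

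It is also fair that the shared thresholds (over 50% Hispanic, over 50% free/reduced lunch) narrow the differences between schools, though they do not remove them. A district with only one drawn school is in one arm under any scheme.

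**Conclusion.** The point holds as a cheap design improvement, not as an error that invalidates the trial. As written, some district with two or more drawn schools would fall wholly in one arm in about one-third to one-half of draws (32-54% for the assumed splits), and some district would have arm counts differing by three or more schools in about 44-47%. The first range depends strongly on the unstated district sizes and is driven by small districts.

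The precision benefit is conditional: roughly 3-5% at a 10% explained share and 7-10% at 20% for vegetable intake, waist and insulin after a 1-df cost, at most 2% for BMI z, and about nil for glucose. It assumes that Table 2's ICCs apply to change and that the factor is fitted in the primary model. The firmer argument is comparability of the arms, which can be secured only before the schools are allocated.

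**What to change.** Replace the allocation sentence with stratified or covariate-constrained randomisation within wave:
- Generate the admissible wave-by-arm allocations. Keep those in which arm counts differ by at most one school in each district and mean percent free/reduced lunch is similar between arms, with the limit set by the trial statistician.
- Check that enough allocations remain and that no pair of schools is always together or always apart. Then draw one at random.
- Add percent free/reduced lunch to the primary model as a school-level covariate (1 df). Consider wave and district as further terms, given the few df.

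The cost is a few hours of programming, a sentence or two in the Protocol, and one or more of the 14 between-school df. No extra schools, visits or data are needed.

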
the year, hosting community engagement demonstrations, (i.e., FV stands, farmer's markets, and recipe demonstrations), and contacting local media outlets to do stories on garden activities/program. Of note, every GLC will likely implement and adapt different strategies from a menu of evidence-based options, which is why we plan to develop a list of these options, and measure these strategies in both intervention and sustainability years as done in the CATCH Travis County study. Forming these GLCs will empower the community members to take ownership in this program and continue to maintain the gardens and sustain the program after the grant cycle is over.

**Edible Gardens:** We have support from school districts and the individual schools to build gardens at each of the school sites. Raised beds will be used at all garden sites, as these are easy to build, make garden access easy for children of all developmental levels, ensure that soils are free of heavy metals/contaminants, and reduce weeds in the garden area. We have support from school districts and the individual schools to build gardens at each of the school sites. Raised beds will be used at all garden sites, as these are easy to build, make garden access easy for children of all developmental levels, ensure that soils are free of heavy metals/contaminants, and reduce weeds in the garden area. The beds will be designed by the GLCs at each school during a “design-build” session with input from the maintenance staff and principals as well as assistance from Texas AgriLife Extension staff and the SFC. Supplies will be purchased from this grant, with the local horticulturist's guidance, and delivered to the appropriate garden site. A garden kick-off event at each garden site will engage students, teachers, practitioners, parents, and community volunteers in a garden build. Each school site will get the materials and supplies needed for garden upkeep (e.g. rakes, hoses, etc.) and for teaching the lessons, (e.g., tables, chairs/benches, cooking grill, portable hand-washing sink, pots/pans, etc.). A big media/kick-off event will be hosted at each school after each garden is built. In addition, the Extension Volunteer Coordinator will place and oversee Master Gardener volunteers who live within each of these communities to assist with the build and upkeep of the garden in the intervention year, as well as subsequent years

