### **TX Sprouts Research Evaluation:**

Evaluation measures will be collected at baseline and end of the school year in both treatments (intervention and control schools). Measurements will occur during the first four weeks of school in the fall and the last four weeks of school in the spring. Most measures on children will be collected at the schools during normal school hours. The fasting blood draws will occur first thing in the morning before school starts. The following evaluation measures will be obtained from students at baseline and post-intervention:

- Measured height, weight, BMI parameters, waist circumference (WC), body composition (via bioimpedance); carotenoid scan of skin
- Blood pressure via child-specific automated cuff;
- Subsample of students will complete three 24-hour diet recalls by telephone;
- Child survey assessing dietary intake via food screener and related determinants of dietary behaviors (e.g., preference/motivation/self-efficacy to eat FV);
- Program lessons may also be audio/visual recorded;
- Voluntary fasting blood sample to assess glucose, insulin, and lipid parameters;
- Accelerometers to measure physical activity;
- Time on Task observations

Parent questionnaires will be handed out or mailed to the homes after consent is obtained at baseline and post-intervention. Questionnaires are translated into Spanish, culturally appropriate, and take ~60 minutes to complete. We will encourage parents to complete the questionnaire before the first family lesson and return it via mail (pre-paid postage will be provided). However, parents will also be able to complete the questionnaire at the first and last lessons. Parent surveys will evaluate the following: food security via USDA validated questions, confidence cooking, dietary intake via validated screener, reported height and weight, medical history, basic demographics, child feeding practices and food home environment from CEBQ and TGEQ, and preferences adapted from Domel et al. We will also attempt to measure height and weight on a subsample of parents, which will occur at the first and last parent lesson. Parent workshops may also be audio/visually recorded.

After the intervention year, we will conduct a series of structured interviews (30 minutes or less per interview) as well as surveys, with participating school stakeholders (i.e., principals, teachers,

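### Consent and baseline come after school allocation and after the intervention gardens are built, and school replacement has no stated cut-off

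*Protocol*

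**What the plan says.** All from the Protocol.

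- **Allocation.** The Year 1 row of Table 1 (4.c Study Timeline) lists "Randomly allocate schools into INT/CON and into waves". Wave 2 has its baseline in Year 3 and wave 3 in Year 4.
- **Gardens.** "Build W1-INT gardens" stands in the summer of Year 1, before wave 1 baseline. "Build W1-CON gardens" stands in the summer of Year 2, after wave 1 post-testing. Waves 2 and 3 follow the same order.
- **Family involvement before baseline.** Under Edible Gardens, a kick-off event brings students and parents into the build. Parents and children may also sit on the Garden Leadership Coalition, which designs the beds. Then: "A big media/kick-off event will be hosted at each school after each garden is built". That second event has no date relative to consent or baseline.
- **Consent and baseline.** The Table 1 note says "Consenting and measurements in the fall will occur the first 2 weeks of school". The Research Evaluation section says "Measurements will occur during the first four weeks of school in the fall and the last four weeks of school in the spring". The fall cell for wave 1 reads "W1 baseline measurements -Implement W1-INT Sprouts program".
- **Parent baseline.** Parents are encouraged to complete the questionnaire before the first family lesson but may do so at that lesson (Research Evaluation). Parent body measurements and blood pressure are taken at the first and last family workshop (5. Measures).
- **Reserve schools.** Sixteen of 18 eligible schools are drawn for allocation, and "the two schools remaining will be used for replacement if a school declines to participate" (4.a Location). No time limit is given.
- **Expected consent.** About 50% of parents (6.e Recruitment).

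**The concern.** Randomising schools makes the eligible children comparable on average. It does not make the volunteers comparable if they volunteer after the arm is known. Here one arm is approached in a school that already has a new garden and the other in a school without one, and about half the families decline. The kind of family that consents can differ by arm, and no description of concealing the arm at consent is given.

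The outcomes are changes from baseline. If intervention families have already helped design or build a garden, part of any effect on vegetable intake, preference or motivation may be in the baseline value and drop out of the change. Of the five primary outcomes this bears mainly on vegetable intake; the psychosocial measures are secondary.

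A school in wave 2 or 3 could decline after learning its arm and be replaced. The replacement would not have been randomised in the same way, and with eight schools per arm each is one eighth of its arm.

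**Working it through.** **Order of events, each wave**

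| Step | Intervention school | Control school |
|---|---|---|
| Allocation | Year 1 | Year 1 |
| Garden built, with students and parents | summer before baseline | summer after post-testing |
| Consent and baseline | fall | same fall |
| Programme | starts same fall | following year |

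Consent and baseline therefore follow both allocation and the intervention garden in all three waves.

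**Baseline window.** Two weeks in the Table 1 note, four in Research Evaluation. These must be reconciled. No date is given for the first lesson, so nothing fixes it after the close of either window.

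**Parent baseline.** Control schools have no family lessons until the following year, so taking parent baseline at the first lesson or workshop has no stated control counterpart, although control parents are to be measured in the same period.

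**The plan's own recruitment figures**

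- 4,800 × 0.50 = 2,400 consenting children, as stated.
- 2,400 × 0.85 = 2,040 completers, as stated.
- 2,040 / 16 = 127.5 per school, stated as 127.

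So about 2,400 of 4,800 eligible children are left out by non-consent.

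**Scale of selection bias (illustration only).** The documents give no consent rate by arm and no link between willingness and outcome. Assumed: consent rates p by arm, and a correlation ρ between willingness to consent and the change score, under a normal selection model.

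Shift in SD units = ρ × [λ(p_con) − λ(p_int)], with λ(p) = φ(z_p)/p.

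- 55% v 45%: 0.396/0.45 − 0.396/0.55 = 0.160, so ρ = 0.1 to 0.3 gives 0.016 to 0.048 SD.
- 60% v 40%: 0.386/0.40 − 0.386/0.60 = 0.322, giving 0.032 to 0.097 SD.

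Multiply by the SD (square root of the within-school variance in Table 2) and divide by the planned effect:

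| Outcome | Variance | SD | Planned effect (absolute) | 55% v 45% | 60% v 40% |
|---|---|---|---|---|---|
| Vegetables (serv/d) | 0.08 | 0.283 | 0.5 | 0.9–2.7% | 1.8–5.5% |
| Glucose (mg/dL) | 40.86 | 6.39 | 2.133 | 4.8–14.4% | 9.6–28.9% |
| BMI z-score | 0.05 | 0.224 | 0.065 | 5.5–16.5% | 11.1–33.2% |
| Waist (cm) | 0.005 | 0.0707 | 0.02 | 5.7–17.0% | 11.4–34.1% |
| Insulin (µU/ml) | 30.41 | 5.51 | 12 | 0.7–2.2% | 1.5–4.4% |

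Example, glucose at ρ = 0.1: 0.016 × 6.39 = 0.102; 0.102 / 2.133 = 4.8%.

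These are absolute sizes. In this model the arm with higher consent takes in less willing families on average, so the sign depends on the sign of ρ; a garden that draws in unusually keen families could act the other way. With equal consent rates the model gives zero, although different kinds of families could still consent in each arm.

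**The case against.** The strongest reply is that families gain no programme access by consenting. Lessons reach all 3rd–5th graders in the school day, consent covers only the evaluation, and control schools are promised the same garden and programme the next year. One information packet is described, with no arm-specific version. This stands as mitigation: it weakens the motive for arm-dependent consent but does not remove it.

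Four stronger readings are tempting and are not supported:

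- *Schools may be replaced at any time.* The Location section does not say so. The sentence fits naturally at the selection stage; its timing is simply open. What stands is the missing cut-off, with all waves allocated in Year 1.
- *Baseline follows the media event.* That event is dated only as after the build. The firmer point is the participatory build, which Table 1 places in the summer.
- *Children's baseline overlaps the lessons.* Table 1 lists baseline before implementation in every fall cell. The two- and four-week windows are an inconsistency, not evidence of exposure.
- *The bias is about 17% of the planned vegetable effect.* If 10 points of keener families join 50%, they are 10/60 = 16.7% of the arm; an extra change of 0.5 serv/d gives 0.083, or 17%. But that assumes an extra change equal to the whole planned effect, 0.5/0.283 = 1.8 SD. The selection model at 60% v 50% gives 0.154 × (0.1 to 0.3) = 0.015–0.046 SD, or 1–3%.

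It is also fair that moving events does not hide a visible garden or put consent before allocation. Consent in Year 1 is not an option for wave 3, since Year 4 third graders are not yet in the eligible grades. Because the kick-off is part of the build, moving family participation may be harder than moving the media event.

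**Conclusion.** The point holds as a design risk. Followed as written, the Protocol allows consent with the arm known, some exposure in intervention schools before baseline, parent baseline at the first lesson, and replacement of a school after allocation. It also states two different baseline windows.

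No bias is demonstrated, and its size cannot be derived from the documents. Under the assumed 55% v 45% consent and correlations of 0.1–0.3 it is small for vegetables and insulin (about 1–3% of the planned effect) and moderate for glucose, BMI z-score and waist (about 5–17%); at 60% v 40% these become about 2–6% and 10–34%. The figures rest on those assumptions and on the Table 2 variances. The change is worth making because analysis cannot restore a baseline taken before exposure or fully undo selection after allocation.

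**What to change.** 1. State one consent and baseline window in both Research Evaluation and the Table 1 note.
2. In each intervention school, hold the media/kick-off event and the first student and family lessons only after that window closes. Where feasible, do the same for student and parent participation in the build.
3. Collect parent baseline before the first family lesson in the intervention arm, and in the same period by an equivalent route in the control arm.
4. Use the two reserve schools only before allocation is drawn. A school that withdraws later is not replaced and is analysed in its allocated arm.
5. Report consent rates and baseline characteristics by arm.

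The cost is rewording Edible Gardens, Research Evaluation, Location, the parent measurement text in Measures and the Table 1 note; a slightly later programme start within a fixed school year that must hold 20 student and nine family lessons; and possibly 15 schools instead of 16 after a late withdrawal. If the summer build cannot move, the other steps still help. Consent would still follow allocation, so selection is reduced and made visible, not removed.
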